## Methods

### Study

The study will take place at Beth Israel Deaconess Medical Center (BIDMC), a Harvard affiliated teaching hospital in Boston, Massachusetts. The care team will include a psychiatrist, social worker, and digital navigator. The psychiatrist and social worker will provide clinical treatment, education, and support for all participants. The digital navigator, as previously discussed, will be available for technology support and mindLAMP training to other care team members and research participants.

For this study, 50 participants will be enrolled and will not be financially compensated for their participation in TECC. Given the success of the pilot Digital Clinic program, including 50 participants is feasible and necessary to collect a diverse sample and see significant effects of different techniques on clinical assessments of depression and anxiety. This study will be open to any adult (18 years or older) who is interested in using smartphone technology to augment their mental health care. Participants are required to meet the criteria for either mild to moderate depression or anxiety as measured on the Patient Health Questionnaire-9 (PHQ-9) or Generalized Anxiety Disorder-7 (GAD-7) scale. Participants must have daily access to a smartphone, be willing to download the mindLAMP app, use their smartphone for mental health care (both in and outside of session time), and be open to learning about an array of clinical modalities (dialectical behavior therapy [DBT], cognitive behavioral therapy [CBT], short psychodynamic therapies). For participants who do not own a smartphone, the care team will help individuals sign up for a free phone through the US Federal Government’s Project Lifeline if they are eligible. Participants must also be affiliated with a BIDMC or Beth Israel Lahey Health provider and be available for eight clinical sessions (telehealth) over the course of 2-4 months. Until the Spanish language version of the mindLAMP app has been properly vetted, participants must be able to read, write, and communicate in English at an eighth grade level. Recruitment efforts for TECC include digital flyers and brief informational sessions for referring providers.

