Stage 1 “Creating the Clinical Foundation”: This stage will allow participants to learn and practice shared decision-making by cocreating treatment goals, identifying thought patterns, and identifying coping skills and defense mechanisms. The goal of this stage is for participants to develop a broad understanding of their thoughts and behaviors while beginning to identify strengths and need areas. Participants will also be introduced to clinical language and definitions for shared language to be established.Stage 2 “Building Clinical Skills”: Expanding from the skills learned in stage one, this stage will focus on teaching and practicing cognitive defusion and behavioral activation techniques. The goal for this stage is to expose participants to practical therapeutic skills that can be used across many situations and symptom management.Stage 3 “Solidifying Clinical Gains”: This stage introduces participants to mindfulness techniques, a diary card–like model, and patient activation and empowerment skills. The purpose of this stage is to ensure participants grasp all technical skills and clinical language reviewed throughout treatment to make informed autonomous decisions regarding treatment preferences.

This yearlong study will follow a prospective longitudinal cohort design where all participants will receive the same treatment and smartphone interventions. Based on our own Digital Clinic pilot data, we hypothesize participants will report a treatment response rate—defined as 50% symptom reduction—of improvements in anxiety and depression within the 8 weeks of treatment compared to their initial baseline. We also hypothesize that both rates of app engagement out of sessions, as well as therapeutic alliance measured during sessions, will be correlated with clinical improvements and suggest a mechanism of action for TECC. Furthermore the study will test the feasibility of providing technology-enabled mental health care within an outpatient clinical setting via virtual telehealth visits, explore the linguistic and cultural appropriateness of the smartphone app (mindLAMP) used in the study, and analyze the symptom changes of anxiety and depression for all study participants.

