### Interventions

Interventions for TECC will be employed through a multipronged approach including in-session care from clinicians, exposure and education to evidence-based therapies, use of the mindLAMP app, and technology support from the digital navigator.

At least 1 week before the initial clinical visit, participants will meet with the digital navigator to download the mindLAMP app, receive app training, and will be asked to begin completing the mood surveys (PHQ-9 and GAD-7) in mindLAMP on a daily basis. During the meeting, participants will be informed the app will not be used to offer emergency services between sessions and app responses will not be monitored outside of clinical sessions. A signed waiver will be presented to reflect this understanding.

The format for TECC sessions will follow the pre-established Digital Clinic structure (Figure 1). Specifically, before each clinical session, participants will be required to complete a variety of clinical surveys. These surveys will be made available through the clinic’s secured, research-based survey platform (REDCap, Vanderbilt University). The surveys (see Figure 2 for more details) are designed to help clinicians develop a comprehensive understanding of each participants progress throughout the study. Once the clinical portion of the session starts, any mindLAMP data collected will be reviewed and discussed. This step will ensure the data in mindLAMP accurately reflects the participant’s lived experience and ensure the personalized nature of each patient’s care is reflected in the session. Next, the clinician will discuss a predetermined clinical skill, and the clinician will work to relate the skill to the patient’s unique needs. The clinician will introduce the skill by describing its purpose, giving examples of when the skill can be used, and explain how the skill could impact the participants mental health needs. With clinician guidance, participants will then practice the skill, brainstorm scenarios in which the skill could be used, and review a skill-building activity (see Multimedia Appendix 1 for details). Activities will be conducted through skill-building modules (eg, mindfulness), informational worksheets, surveys, and free-writing opportunities that will be available through the app. Participants will be encouraged to complete the activities between sessions to strengthen their understanding and comfortability of use with each skill.

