**Figure 3 figure3:**
[figure not shown]
Screenshots of mindLAMP showing the Learn, Assess, Manage, and Prevent functions.

At the end of the study, participants will be provided a paper or electronic packet of all therapeutic skills learned, activities practiced, and mindLAMP data collected. Participants will also be allowed to keep using the app as a self-help tool or delete the app completely. A copy of clinical metrics and results will be offered to participants’ referring provider to ensure transparency and continuation of care. In general, TECC clinical sessions and digital navigator meetings can be conducted in person or through a video platform. However, due to COVID-19, all TECC-related participant meetings for the next year will be held over a Health Insurance Portability and Accountability Act–compliant video platform to maintain social distancing practices.

As previously mentioned, TECC follows an eight-session template (Figure 4), which provides a step-by-step guide for participants, clinicians, and digital navigators.

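### Part of the stated reason for 50 participants, seeing effects of different techniques, cannot be met when everyone receives the same skills in one fixed order

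*Protocol article*

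**What the plan says.** The Study subsection of Methods sets the number: "For this study, 50 participants will be enrolled". It introduces the reasons with "Given the success of the pilot Digital Clinic program, including 50 participants is feasible and necessary" and gives two purposes, a diverse sample and the ability to "see significant effects of different techniques on clinical assessments of depression and anxiety". The grounds for 50 are thus feasibility, diversity and technique effects.

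On design, the Introduction describes a "prospective longitudinal cohort design where all participants will receive the same treatment and smartphone interventions". Under Interventions, in each session "the clinician will discuss a predetermined clinical skill". Later in the same subsection, "TECC follows an eight-session template (Figure 4), which provides a step-by-step guide for participants, clinicians, and digital navigators". The headings Session One to Session Eight then name one skill each: shared decision making, thought patterns, coping skills and defense mechanisms, cognitive defusion, behavioral activation, mindfulness, the skills card, and patient activation.

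The Analysis subsection plans an effect size for TECC on stress, anxiety and depression symptoms. It adds regressions on baseline factors, working alliance and technology engagement, and a comparison with a matched control group. It describes no contrast between techniques.

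**The concern.** One of the reasons for the sample size is a property that the described design lacks. To see the effect of one technique as distinct from another, technique exposure must vary in a way not tied to something else that moves the scores. Here the schedule ties technique to session for every participant. A change after the defusion session may reflect defusion, but equally the three earlier skills, four sessions of clinician contact, natural recovery, or regression to the mean in people enrolled because they scored on a symptom scale.

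What is at stake is what may be concluded. PHQ-9 and GAD-7 are completed daily in the app, so movements around each session will be visible. The Results section says the findings will be used to support or adapt the care model. With the clause in place, a reader could take such movements as evidence for keeping or dropping individual modules, and could believe the study was sized for that.

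**Working it through.** **1. Can the stated 50 be reproduced?** No. The article gives no significance level, power, expected change, SD, response rate or dropout figure. An article may leave these to the full protocol, so their absence is not counted here. The question is whether the technique clause fits the design described.

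**2. Are scheduled technique effects identifiable?** Inputs: 8 skills in fixed order, one per session (Session One to Session Eight). Take 9 occasions, baseline plus 8 sessions. Give each occasion its own effect (9 columns), and give each technique an indicator that switches on at its session and stays on (8 columns), making 17 columns.

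- Under the fixed order, the indicator for technique k equals the sum of the occasion columns from k to 8. All 8 technique columns are exact combinations of the 9 occasion columns.
- Rank of the design matrix: 9 of 17 at N = 50, 9 of 17 at N = 500, 9 of 17 at N = 2000. More participants add nothing.
- For illustration only, with the order randomized among 50 participants the rank is 16 of 17, and all 7 between-technique contrasts become estimable. The fixed common order, not the number, is the cause.

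This models the scheduled skill only. It does not include differences between people in app practice. Sessions may be spread over 2-4 months; that variation could help separate calendar time from session number, but not technique from session number.

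**3. What can 50 deliver for the whole package?** Assumptions, none of them in the article: two-sided 5% level, 80% power, 50 completers or 40 (20% loss), a matched cohort of 50, and a response rate of 50%.

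- *Pre-post change*, in SDs of the change score. Normal approximation: (1.960 + 0.842)/√n. For n = 50, 2.802/7.071 = 0.396; for n = 40, 2.802/6.325 = 0.443. The paired t-test gives 0.404 and 0.454.
- *Against the matched cohort*, in SDs of the outcome: (1.960 + 0.842) × √(2/50) = 2.802 × 0.200 = 0.560.
- *Response rate*: the Wilson 95% interval for 25/50 is 36.6% to 63.4%, a half-width of 13.4 points.

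The 50% in the Introduction defines response for one person as a symptom reduction of that size. It is not an expected response rate, so the 50% used here is only a convenient value near which the interval is widest.

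**The case against.** The strongest reply is that nothing in the plan rests on the clause. The Objective is feasibility, practicality for people with limited English proficiency, and effectiveness of the TECC design. The hypotheses concern response against baseline and correlations with engagement and alliance. The analysis targets TECC. The phrase may simply mean a package made up of different techniques. This stands as far as severity goes: if the package was meant, the sentence is a wording fault, and the same edit cures it.

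The second reply is that technique exposure does differ between people. Between-session activities are encouraged rather than required, app elements are matched to the individual, time on each element is logged, and symptom change will be related to engagement patterns. A reader might infer from the fixed order that the study holds no information at all about techniques. The documents do not support that: exploratory associations are possible. They are self-selected, however, and the article does not tie the 50 to them.

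A reader might also infer that the plan will credit session-by-session changes to particular skills. It does not say so; the Analysis subsection plans no such attribution. The misreading is a risk left open by the clause, not a planned step.

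**Conclusion.** The point holds as a correction to a stated rationale and to the conclusions it permits. Separate, attributable effects of the scheduled techniques are aliased with session number, elapsed time and carry-over at any sample size, so they cannot be a reason for choosing 50.

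It would go too far to say that 50 is the wrong number or has no justification. Feasibility after the pilot and a diverse sample are also given as grounds, and they are untouched. Under the assumptions labelled in the working, 50 is reasonable for a moderate whole-package pre-post change (about 0.40, or 0.45 with 40 completers). It is less sensitive for the matched comparison (about 0.56, if that cohort also has 50). The identifiability result needs none of those assumptions; it follows from the fixed common order alone. This is not a design failure that must be repaired before the study can run.

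**What to change.** In Methods, Study, delete the technique-effects clause and keep the feasibility and diversity grounds. In its place, state what 50 gives for TECC as a whole, with the assumptions named. For example: with a two-sided 5% level and 80% power, 50 completers allow detection of a standardized pre-post change of about 0.40 (0.45 with 40 completers) and a standardized difference of about 0.56 from the matched cohort if it also numbers 50; a response rate near 50% would be estimated to within about 13 points either way. Since 50 was already chosen, present these as what the number delivers, not as how it was derived.

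In Analysis, add that session-by-session scores are a descriptive time course, and that associations with use of app elements are exploratory and not evidence for individual techniques.

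The cost is a few sentences and a less favourable claim. No participants, procedures, outcomes or planned models change.

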### Interventions

Interventions for TECC will be employed through a multipronged approach including in-session care from clinicians, exposure and education to evidence-based therapies, use of the mindLAMP app, and technology support from the digital navigator.

At least 1 week before the initial clinical visit, participants will meet with the digital navigator to download the mindLAMP app, receive app training, and will be asked to begin completing the mood surveys (PHQ-9 and GAD-7) in mindLAMP on a daily basis. During the meeting, participants will be informed the app will not be used to offer emergency services between sessions and app responses will not be monitored outside of clinical sessions. A signed waiver will be presented to reflect this understanding.

The format for TECC sessions will follow the pre-established Digital Clinic structure (Figure 1). Specifically, before each clinical session, participants will be required to complete a variety of clinical surveys. These surveys will be made available through the clinic’s secured, research-based survey platform (REDCap, Vanderbilt University). The surveys (see Figure 2 for more details) are designed to help clinicians develop a comprehensive understanding of each participants progress throughout the study. Once the clinical portion of the session starts, any mindLAMP data collected will be reviewed and discussed. This step will ensure the data in mindLAMP accurately reflects the participant’s lived experience and ensure the personalized nature of each patient’s care is reflected in the session. Next, the clinician will discuss a predetermined clinical skill, and the clinician will work to relate the skill to the patient’s unique needs. The clinician will introduce the skill by describing its purpose, giving examples of when the skill can be used, and explain how the skill could impact the participants mental health needs. With clinician guidance, participants will then practice the skill, brainstorm scenarios in which the skill could be used, and review a skill-building activity (see Multimedia Appendix 1 for details). Activities will be conducted through skill-building modules (eg, mindfulness), informational worksheets, surveys, and free-writing opportunities that will be available through the app. Participants will be encouraged to complete the activities between sessions to strengthen their understanding and comfortability of use with each skill.

**Figure 1 figure1:**
[figure not shown]
The Digital Clinic program structure including pre- and postclinical activities.

**Figure 2 figure2:**
[figure not shown]
The Technology Enabled Clinical Care survey and data collection timeline. BASIS-24: Behavior and Symptom Identification Scale-24; GAD-7: Generalized Anxiety Disorder-7; PC-PTSD-5: Primary Care Posttraumatic Stress Disorder-5; PHQ-9: Patient Health Question-9; SUS: System Usability Scale; TAM: technology acceptance model; WAI-SF: Working Alliance Inventory–Short Form; WHO-5: World Health Organization Five.

Upon completion of each clinical session, participants will meet with the digital navigator to address any technology-related questions or issues. The digital navigator will also work with participants to create any additional mood-tracking surveys and retrieve smartphone senor data (if applicable). The mindLAMP app will be used in and outside of the session to allow participants to track their daily moods (PHQ-9 and GAD-7 scales) and practice clinical skills (through activities in the app).

As previously mentioned, the mindLAMP app will be used to provide digitally augmented care [24]. Cocreated with patients and clinicians, mindLAMP is designed not to drive care decisions or protocolize treatment but, rather, to serve as a flexible tool to be deployed in a personalized manner to customize care for each person. To support this flexibility, mindLAMP allows users to create unique surveys specific to their needs and assign a schedule of times to be reminded [25]. Likewise, mindLAMP can capture diverse sensor data from the smartphone, ranging from step count, sleep, geolocation, and screen time, and the user can determine which, if any, are useful to capture. As an example, some patients may wish to track mood and sleep to determine if changing their sleep pattern may improve their mood [26]. Any use of such data will be determined by clinical needs and not the TECC protocol. mindLAMP also offers options for app interventions and supports a suite of resources that are customizable to the unique needs of users. The learning tab presents relevant tips and information, and the management tab has a series of tools and skill-building modules like mindfulness, defusion (from acceptance and commitment therapy [ACT]), goal setting, medication reminders, and emergency planning. Not all learning and management offerings will be relevant, or even useful, for all patients, and the goal of care is to help match the right elements of mindLAMP at the right time for each patient—much like in traditional medication management or therapy care. As a tool, mindLAMP aims to be accessible on Apple and Android smartphones as well as on an internet browser (ie, computers) and can support multiple languages including Spanish and English. In this protocol, mindLAMP is used in a structured manner, with each week using different aspects of the app, but personalization and customization are still part of each week’s use, as outlined in later sections. Figure 3 provides several examples of the mindLAMP interface. A set of handouts is also included in Multimedia Appendix 1 that can be used as nondigital *backups*, in case a patient has a technical issue, and can be mailed or emailed to each patient in TECC.

**Figure 3 figure3:**
[figure not shown]
Screenshots of mindLAMP showing the Learn, Assess, Manage, and Prevent functions.

At the end of the study, participants will be provided a paper or electronic packet of all therapeutic skills learned, activities practiced, and mindLAMP data collected. Participants will also be allowed to keep using the app as a self-help tool or delete the app completely. A copy of clinical metrics and results will be offered to participants’ referring provider to ensure transparency and continuation of care. In general, TECC clinical sessions and digital navigator meetings can be conducted in person or through a video platform. However, due to COVID-19, all TECC-related participant meetings for the next year will be held over a Health Insurance Portability and Accountability Act–compliant video platform to maintain social distancing practices.

As previously mentioned, TECC follows an eight-session template (Figure 4), which provides a step-by-step guide for participants, clinicians, and digital navigators.

**Figure 4 figure4:**
[figure not shown]
Overview of clinical sessions (left) and session-specific checklist (right).

### Session One: Shared Decision Making

As with most initial therapeutic sessions, a client assessment will be completed, a safety plan created, and feasibility of short- and long-term goals will be addressed. (Please note, the safety plan used in TECC was not created by members of the research team and was borrowed from our affiliated hospital’s psychiatric department.) Figure 5 shows an example of how the safety plan can appear in mindLAMP. After safety planning, the study time frame, expectations, and structure will be reviewed with participants. Since the study will be providing clinical treatment in a time-limited manner, the need for supplemental case management services will also be evaluated, and education and resources may be provided; however, connections to services cannot be guaranteed. For the remainder of the session, the skill of shared decision making (SDM) will be discussed.

